**Table 1 Tab1:** **Scenario planning - power calculations undertaken to inform the sample size**

Scenario	Re-abuse Rate % Control	Re-abuse Rate % SAAF	Unclustered total sample size	Design effect	Clustered total sample size (rounded)
1	50	40	800	1.5	1,200
2a	25	15	510	1.5	770
2b				2.0	1,000
3a	10	5	900	1.5	1,300
3b				2.0	1,800
4a	10	2.5	400	1.5	600
4b				2.0	800
5a	20	10	400	1.5	600
5b				2.0	800

Given the uncertainties in the CIN data, and in the absence of an existing, secure ICC from other studies, we judged that a design effect of 2.0 was most appropriate given the rate of repeat CPPs. This points to the need for an achieved sample size of 1,800 cases, which we estimate will be achieved within a 6-month period following the training of the experimental social workers in each CSD.

The design of the study, including reliance on administrative data, attenuates the need to factor dropout into the calculations.

### Recruitment

The six sites listed above were recruited by the DfE, in consultation with the study team. A total of 19 CSDs were approached by the DfE and the 6 included sites were those that expressed an interest and had capacity.

### Assignment of interventions

*Sequence generation*: social work teams within participating LAs will be randomly allocated to one of the two study arms. The allocation will be achieved by computer generated random numbers by the Northern Ireland Clinical Trials Unit (NI CTU) using randomly permuted blocks.*Allocation concealment*: the NI CTU will inform the PI and Trial Manager of the allocation of each social work team. The Trial Manager will then Email the designated contact person in each CSD to inform them of their allocation.The Trial Manager will also inform Children and Family Training, who will then liaise directly with the CSD to arrange training for those social workers/teams in the experimental arm.*Implementation*: the allocation to the intervention or control arm will be generated by the NI CTU and conveyed securely to the Trial Manager and PI.*Check on baseline equivalence*: all social workers will complete a baseline questionnaire prior to randomisation, which will provide information on their experience, training to date, expectations of the training, attitudes towards the trial, and so on. This will provide some indication of baseline equivalence between the two arms, as well as informing the interpretation of the study results.*Blinding*: given the nature of the intervention, the data to be collected, and the interface with the Trial Manager (who will be the point of contact for enquiries regarding data collection), it will not be possible to maintain the concealment of allocation, that is social workers will know whether or not they have been trained. Further, the Case Report Form will include questions about the use of the SDM tools (which the control group social workers will not be using) and the assessments that will be quality assessed may include indications that the authors were in receipt of training/used the SAAF SDM tools.

However, we will endeavour to select assessments for audit without divulging the arm from which they were sourced to those conducting the quality assessment. Each CSD will be asked to provide between 25 and 40 assessments, randomly selected by the NI CTU, from participating social workers in each arm, and make these available to the researchers undertaking the quality audit, without divulging which teams the authors belong to.

We will also include a question on the quality assessment schedule that will enable assessors to indicate whether or not the assessment led them to believe it had been undertaken by a social worker in the SAAF (experimental) arm.

#### Implementation evaluation

Given that this is a complex intervention, we are conducting an implementation evaluation alongside the effectiveness study, informed by the emerging field of implementation science [7–10]. We will conduct an online survey of social workers in the experimental arm to explore whether SAAF was implemented as intended, their perceptions of SAAF, how easy it was to use, how relevant and useful. We will explore the extent to which staff felt sufficiently skilled to learn and use SAAF, whether and how it was embedded in working practice, the processes and resources they feel were necessary for its successful implementation, including buy-in from managers and other key stakeholders (and whether any of these were not in fact in place). These data will also be used to explore the possible reasons for differences across the participating CSDs. The online survey will be supplemented with a number of in-depth interviews with key stakeholders from each CSD to explore implementation in more detail. Control group social workers will also be surveyed by means of a short, on-line questionnaire to ascertain detailed information about management as usual.

In order to explore the perceived impact of training, social workers in the experimental group will be asked to complete a second questionnaire following the SAAF training to explore its impact on their perceived knowledge and skills in assessment.

#### Data on baseline equivalence

In order to explore the extent to which randomisation has created two equal groups, the study will collect relevant data from participating social workers on their qualifications, experience and confidence in relation to complex assessments, and knowledge in relation to key areas (for example, mental illness, intimate partner violence, substance misuse). These data will be collected from all social workers following a study briefing.

### Data management

Case Report Forms will be completed on-line by social workers, using a unique identifier for both the social worker and the family. All data will be stored securely and no identifying details of the family/child will be recorded.

The DfE will flag each child whose assessment is used in the trial to facilitate later follow up, should funding be available. These data will remain anonymised (that is no child’s name would be used).

All data will be monitored using central statistical monitoring for consistency, viability and quality.

Data from the study will only be presented in public once the main results are published in peer reviewed journals according to Consolidated Standards of Reporting Trials (CONSORT) guidelines and disseminated to all the study participants (CSDs) in an accessible format.

### Data analysis

#### Assessing trial validity

Initial data analysis (descriptive statistics and bivariate tests) will examine the extent to which the necessary conditions required to permit a valid test of the efficacy of SAAF have been met [11]. This will include assessment of the achieved statistical power, patterns of attrition (social workers leaving/moving), between-group equivalence on key factors (for example, staff turnover, team size, experience of social workers, types of cases), SAAF fidelity (the extent to which SAAF appears to have been used as intended) and discriminability (for example, the approach to assessment undertaken by control social workers is sufficiently distinct).

#### Assessing the effectiveness of SAAF

##### Intention-to-treat analyses

The primary outcome analysis will be an intention-to-treat analysis (ITT) such that all cases will be assessed in accordance with the randomisation. Analysis will be conducted both within and across LAs. We will maximise use of administrative data in order to document the extent of differences between the experimental and control groups.

##### Outcome measures

Some outcome measures are binary and some are continuous. Estimation methods will vary depending on whether the dependent variable is binary or continuous, but the logic of the analysis will in each case be the same.

##### Inclusion of covariates

In addition to the standard ITT, multivariate (ordinary least squares (OLS) and logistic regression) models will be estimated to examine the impact of covariates on outcomes. Baseline outcome measures (for example, type of abuse, risk factors identified) will be included as covariates to allow for individual differences, and site differences will be modelled. Including information on covariates will allow us to examine moderator effects and to begin to unpick the mechanisms through which SAFF might impact on improved assessments and associated outcomes.

A key part of this analysis will be to try to minimise the unexplained variance in site-specific effects. This will increase power and, by capturing the factors that explain why effects vary across sites, will help in generalising the results beyond the study sites. Thus, we will look at possible sources of variation across sites - in participant characteristics, in staff experience and in what constitutes management as usual; for example, including site-specific averages as controls in regression analysis.

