### Intervention and comparison

#### Experimental group: Safeguarding Children Assessment and Analysis Framework (SAAF)

The SAAF assessment tool asks social workers to make a judgement relating to each of 55 items that social workers should consider when making their assessments:

 For 33 items these are judgements of level of risk or concern (both terms are used), covering the child’s developmental needs, parenting capacity and family and environmental factors. Whilst explicitly not a score card, social workers are asked to rate each item on a five-point Likert-type scale, one end of which represents ‘low level of concern’ and the other ‘high level of concern’. For 22 items these are judgements about prospects for intervention, covering parenting capacity, family and environmental factors, and child’s developmental needs. Again, this is not a score card. Social workers are asked to indicate where, again on a five-point scale, they judge the prospects for (successful) intervention to lie, with ‘reasonable prospects of success’ at one end, and ‘poor prospects’ at the other.

Social workers are then asked to make three summative judgements, using a three-point scale:Level of harm (low, moderate, high);Level of risks of re-abuse or likelihood of future harm (low, moderate, high level of risks); andProspects for successful intervention (poor, moderate, better prospects).

This is then used as a basis for guiding decision-making.

The SAAF approach to assessment and analysis will be taught to social workers in the experimental arm in a two-day training course by SAAF’s developers - *Children and Families Training*. Social workers who attend SAAF training will receive the following:

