### Outcomes

#### Primary outcome

Differences between the two arms in the proportion of cases resulting in maltreatment or recurrence of maltreatment following the completion of an assessment (S17 cases) or initial child protection conference (S47 cases).

*Measures*: using administrative data (CIN data^b^) collected by LA CSDs we will assess the (re)occurrence of maltreatment, as defined by:

 Number of children who become subject to a CPP for a second or subsequent time (or for the first time following a S47 or S17 assessment that did not result in a CPP), as a result of concerns linked to the original assessment; Number of reassessments or re-referrals as a result of concerns linked to the original maltreatment/perceived risk of maltreatment;

At a national level, the CIN data include items such as ‘Initial category of abuse’ and ‘Latest category of abuse’. In order to determine whether or not the trigger incidents are related, that is are indicative of a failed plan or inadequate assessment, data are needed that provide information at a more granular level than that typically collected for the National Statistics Office (the annual CIN return^c,d^). For this purpose we will use the more detailed data gathered by the CSDs (information management) and collect data immediately post-assessment from social workers *via* an electronic questionnaire (the Case Report Form). These data will provide us with information about the concerns of social workers, their confidence in their assessments, their plans and assessments of future risk. They will also ensure that i) we do not miscategorise apparently unconnected events that in fact have a common underlying cause. For example, physical abuse by a parent and sexual abuse by a stranger *may* be unrelated, but they may also be symptoms of a seriously neglectful environment; ii) we can link children who move between one form of assessment or focus to another; for example, S17 to S47, and monitor associated changes in assessment.

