### Study timeline

The trial formally commenced on 2 January 2014 (contract agreed). Recruitment by the DfE took place between December 2013 and April 2014.Following a study briefing session, social work teams in each of the participating CSDs will be randomised between May and August 2014. Social workers in the experimental arm in each CSD will receive training in SAAF in groups of 20. Once training is complete in a CSD, all social workers in that CSD will be required to provide information on each of the assessments they complete for a period of 6 months. The flow of work is not always predictable, and this period may be extended in order to obtain the necessary number of cases needed, or foreshortened in the even that this target is reached sooner. Figure 1 provides details of the timeline for each participating CSD.

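### The covariate-adjusted models treat risk factors identified during the assessment as baseline, although they are recorded after randomisation and SAAF is meant to change them

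*Protocol article*

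**What the plan says.** The Intention-to-treat analyses section sets the primary analysis: "The primary outcome analysis will be an intention-to-treat analysis (ITT) such that all cases will be assessed in accordance with the randomisation". The Inclusion of covariates section then adds further models: "In addition to the standard ITT, multivariate (ordinary least squares (OLS) and logistic regression) models will be estimated". Of the covariates in them it says: "Baseline outcome measures (for example, type of abuse, risk factors identified) will be included as covariates to allow for individual differences". The same paragraph gives them another purpose, to examine moderators and "to begin to unpick the mechanisms through which SAFF might impact on improved assessments and associated outcomes".

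On timing, the Study timeline section says that "social work teams in each of the participating CSDs will be randomised between May and August 2014", with training of the SAAF teams to follow. Cases come after that: "Once training is complete in a CSD, all social workers in that CSD will be required to provide information".

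On source, the Primary outcome section draws on departmental records and on a Case Report Form, with a plan to "collect data immediately post-assessment from social workers". The form covers the worker's concerns, confidence, plans and view of future risk.

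On what SAAF acts on, the intervention section states: "For 33 items these are judgements of level of risk or concern". The Primary aim section hypothesises that SAAF workers will assess risk more accurately.

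**The concern.** A covariate can safely sharpen a randomised comparison if it is fixed before allocation, or at least recorded without influence from it. Risk factors identified in the assessment meet neither condition. The worker who identifies them already knows the arm, and in the SAAF arm has been trained to look for and weigh risk differently.

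Two things can then go wrong. If SAAF detects risk in families that control workers would miss, the identified families are not alike across arms, and neither are the unidentified ones. Stratifying or adjusting on identification compares unlike groups and can produce an apparent effect where there is none. If instead SAAF works because it identifies risk that is then acted on, adjustment removes part of the real effect.

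The paragraph also asks one set of covariates to do two jobs: to remove individual differences, which calls for variables unaffected by arm, and to explain mechanism, which calls for variables that are affected. A reader of the adjusted odds ratio could not tell which job it had done.

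**Working it through.** **Timing.** The order in the Study timeline is randomisation of teams, training, then case reporting. No trial case is assessed before allocation. The only data stated to be collected before randomisation are a worker questionnaire (Assignment of interventions, check on baseline equivalence), which is not at case level.

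**Source.** *Risk factors identified* is by its wording a result of assessment, and SAAF has 33 items on risk or concern. *Type of abuse* is less clear. The Primary outcome section notes that the national data hold an initial and a latest category of abuse, and the covariate section does not say which would be used.

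**Illustration under no true effect.** The plan gives no figure for this bias, so every input here is assumed, apart from the 10% control re-abuse rate, which is scenario 3 of Table 1.

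First case: a risk factor is truly present in 40% of families. Re-abuse is 15% with it and 6.67% without, so 0.4 × 0.15 + 0.6 × 0.0667 = 10% in both arms. Control workers flag it with sensitivity 50% and false-positive rate 10%; SAAF workers with 80% and 30%.

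- Control, flagged share: 0.4 × 0.5 + 0.6 × 0.1 = 0.26. Re-abuse if flagged: (0.20 × 0.15 + 0.06 × 0.0667)/0.26 = 13.1%. If not flagged: (0.20 × 0.15 + 0.54 × 0.0667)/0.74 = 8.9%.
- SAAF, flagged share: 0.4 × 0.8 + 0.6 × 0.3 = 0.50. Re-abuse if flagged: (0.32 × 0.15 + 0.18 × 0.0667)/0.50 = 12.0%. If not flagged: (0.08 × 0.15 + 0.42 × 0.0667)/0.50 = 8.0%.

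The odds ratios are 0.906 in the flagged stratum and 0.888 in the other. A logistic regression of outcome on arm and flag, fitted to the expected counts, gives 0.896. The unadjusted odds ratio is exactly 1.00.

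The same calculation with other assumed inputs (prevalence 40% throughout):

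| Sensitivity/false-positive %, control v SAAF | Re-abuse with v without factor | Adjusted odds ratio (truth 1.00) |
|---|---|---|
| 50/10 v 80/30 | 20% v 3.33% | 0.801 |
| 50/10 v 80/30 | 15% v 6.67% | 0.896 |
| 50/10 v 80/10 | 15% v 6.67% | 0.933 |
| 50/0 v 70/0 | 15% v 6.67% | 0.942 |
| 50/10 v 60/10 | 15% v 6.67% | 0.980 |
| 50/10 v 60/5 | 15% v 6.67% | 0.995 |
| 50/10 v 50/10 | 15% v 6.67% | 1.000 |

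The last row shows that the bias comes only from identification differing between arms.

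**Illustration with a true effect.** A large simulation (2,000,000 cases, no clustering) assumed that half of families are high-risk, with recurrence 16% v 4%. Risk was identified in 50% of high-risk control families and 60% to 90% of high-risk SAAF families, with 10% false identification in both arms.

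- No true effect: the adjusted odds ratio falls to 0.967 (60%) through to 0.841 (90%).
- Recurrence halved by a route other than identification: unadjusted about 0.47 to 0.48; adjusted 0.458 to 0.404, an exaggeration.
- Effect wholly through identification (recurrence in identified high-risk families cut to one tenth): unadjusted 0.871 to 0.535; adjusted 0.916 to 0.656, a dilution.

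**Scale against sampling error.** The target is 900 × 2.0 = 1,800 cases, so 900 per arm with 1:1 allocation assumed. At 10% in both arms, the standard error of the log odds ratio is √[2.0 × 2/(900 × 0.10 × 0.90)] = √(4/81) = 0.222. A bias to 0.896 (log −0.110) is about half a standard error; a bias to 0.801 (log −0.222) is about one. More cases would not reduce it.

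**The case against.** The strongest reply is that the main result is safe. A reader might infer that the trial's primary estimate is biased. The documents do not support that: the primary analysis is by randomised arm, and the covariate models are expressly additional to it. The multilevel models for between-group differences are not stated to contain these covariates either, so they are exposed only if they are given them.

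A reader might also infer that both named covariates are products of the intervention. That is not established for type of abuse. It has no stated source, and an initial category set at referral, generally by intake or single-point-of-entry teams outside the trial, might not depend on arm. Nor does the ancillary analysis by severity of initial maltreatment clearly share the fault. It asks whether recurrence varies with severity; no severity-adjusted SAAF effect is stated, and severity has no stated source.

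The size is also open to challenge. The two largest distortions in the table triple the false-positive rate under SAAF and leave overall classification accuracy at 74% in both arms, which fits poorly with the hypothesis of more accurate assessment. With false positives held at 10%, the first case gives 0.933, and the flagged stratum then looks worse under SAAF (13.7% v 13.1%). It is therefore not a general rule that SAAF looks better in both strata.

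Finally, studying mechanism with assessment-derived variables is legitimate. What remains is that the paragraph also commits to these variables as baseline adjusters. That is a stated choice, not a detail left to an analysis plan.

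**Conclusion.** The point holds for *risk factors identified*, and for *type of abuse* if it comes from the trial worker's assessment. Calling such a variable baseline is wrong on the protocol's own timeline. Entering it to allow for individual differences means that the supplementary adjusted SAAF effect is no longer an estimate of the total randomised effect. The primary intention-to-treat comparison stands.

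The bias can exaggerate or dilute the effect. Its size is unknown. Under assumed differential identification, a true odds ratio of 1.00 moves to about 0.80 to 0.99, which is at most about one standard error at the planned sample size under those inputs. The conclusion rests on identification differing between arms, which is what SAAF is designed to bring about. If it did not differ, adjustment would do almost no harm.

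**What to change.** Reword the Inclusion of covariates section so that models estimating the SAAF effect, including any multilevel model, adjust only for:

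- site;
- social-worker characteristics from the questionnaire completed before randomisation;
- case data fixed before the trial team's assessment, for example child age, prior Child Protection Plan or referrals, and abuse category as recorded at referral, where the department's record holds them.

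State the source and time of recording for type of abuse. Move *risk factors identified* and other assessment-derived variables to a separate exploratory mechanism analysis, labelled post-randomisation.

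The 1,800-case target does not change. The costs are some loss of prognostic adjustment and the need to confirm that each department holds usable referral-stage fields. The article does not show that it does, and it says that the national data are hard to interpret. It is also worth confirming that intake teams are outside the trial at every site, since the eligibility section excludes them only as a general rule.

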## Methods

### Study sites

Six CSDs in England have been recruited by the DfE (Leeds, Oldham, Nottinghamshire, Greenwich, Bournemouth and Hampshire). These represent different CSD types (unitary, county, and metropolitan) located in a range of geographical areas (North West, Yorkshire and Humber, East Midlands, South East, South West and London).

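### Site averages entered as controls cannot show why the SAAF effect varies across sites, which is the purpose the protocol gives them

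*Protocol article*

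**What the plan says.** The relevant text is in the protocol article, Data analysis, Inclusion of covariates. It describes models fitted in addition to the standard intention-to-treat analysis.

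- The aim: "A key part of this analysis will be to try to minimise the unexplained variance in site-specific effects".
- The promised benefit, besides more power: "by capturing the factors that explain why effects vary across sites, will help in generalising the results beyond the study sites".
- The device, offered as the way to look at participant characteristics, staff experience and the content of usual management: "for example, including site-specific averages as controls in regression analysis".
- On moderation: "Including information on covariates will allow us to examine moderator effects and to begin to unpick the mechanisms".
- On site itself, only that "site differences will be modelled"; the form is not given.

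Other sections bear on this. Study sites: "Six CSDs in England have been recruited by the DfE". Study design stratifies the randomisation of teams by site. Intention-to-treat analyses plans results for each local authority as well as overall. Multilevel models offers random effects, where suitable, alongside a fixed-effect comparison, and accounts for cases being clustered in teams. None of these sections names an arm-by-covariate term, an arm-by-site term or a SAAF effect that varies randomly by site.

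**The concern.** The question posed is one of moderation: what makes SAAF work better in one department than in another. The device named answers a different question: what makes outcome levels higher or lower in one department than in another. The two have different null hypotheses, and one can be true while the other is false.

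An analyst who follows the text could report that a factor explains where SAAF works when it explains only where maltreatment is recorded more often. Equally, an analyst could find no role for a factor that does change the SAAF effect. The protocol calls this a key part of the analysis and says it will help carry the findings beyond six departments, so a misattribution would reach the advice given to other departments.

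**Working it through.** **Inputs.** Six sites (Study sites). 1,800 cases, and 10% against 5% in scenario 3 (Sample size, Table 1). Design effect 2.0 (same section). The protocol states no figure for this analysis, so there is none to reproduce. All slopes below are assumptions.

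**Step 1: algebra.** Let x be the site average for a site and t the arm (0 or 1).

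- Control only: logit(p) = a + b·t + g·x. The site's SAAF contrast is (a + b + g·x) − (a + g·x) = b, the same at every site whatever g is. A site intercept cancels in the same way.
- With an arm-by-factor term d·t·x, the contrast is b + d·x, which can differ by site.

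**Step 2: exact example (linear scale).** Put x at −1.25, −0.75, −0.25, 0.25, 0.75, 1.25 and let the site effect be −0.05 + 0.03x. The variance of x is 2 × (1.5625 + 0.5625 + 0.0625)/6 = 0.7292, so the variance of the site effects is 0.0009 × 0.7292 = 0.00066. Variance left unexplained:

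- arm only: 0.00066
- arm + site average: 0.00066
- arm + site average + arm × site average: 0

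The level slope drops out, so its value does not matter here.

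**Step 3: what a significant control means.** Simulation with 150 cases per site and arm (6 × 2 × 150 = 1,800), 10% against 5% at x = 0, 1,000 runs, no team variance. In an additive model the control's coefficient is roughly an information-weighted average of the two arm slopes. The weights are 0.10 × 0.90 = 0.09 and 0.05 × 0.95 = 0.0475, so the SAAF share is 0.0475/0.1375 = 0.345. The pooled slope is therefore about (control slope) + 0.345 × (SAAF slope − control slope).

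| Control slope | SAAF slope | Effect varies? | Pooled slope | Control significant | Interaction significant |
|---|---|---|---|---|---|
| 0 | 0 | no | 0 | 6.0% | 5.1% |
| 0.4 | 0.4 | no | 0.40 | 96.5% | 5.2% |
| −0.3 | +0.4 | yes | −0.06 | 8.0% | 89.2% |
| 0 | +0.6 | yes | 0.21 | 54.2% | 77.4% |

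The control responds to the pooled slope, whether or not the effect varies.

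**Step 4: sensitivity to the slopes.** Fix the effect slope at 0.5 per SD of the factor. The pooled slope is then (control slope) + 0.17, and it cancels near a control slope of −0.17. Simulated rates at which the control is significant:

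- control slope −0.20 to −0.15: 6% to 9% (the interaction: 72% to 76%)
- control slope 0: 45% to 52%
- control slope +0.15: 92% to 95%
- control slope −0.4: 72%

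**Step 5: clustering.** The interaction rate of about 5% in Step 3 holds only because no team variance was simulated. If the variance is doubled (design effect 2.0, assumed to apply to this term) and the model ignores it, the critical value is effectively 1.96/√2 = 1.386, and the two-sided rejection rate is about 16.6%. Simulations with a design effect near 2 gave 13% and about 14% under a constant effect.

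**Step 6: collinearity, if site is coded by indicators.** Six indicators + arm + site average make 8 columns of rank 7, so the site average is redundant. Replacing it with arm × site average gives 8 columns of rank 8, which is estimable. Six sites leave 6 − 1 = 5 site-level contrasts for all candidate factors together.

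**The case against.** **The device is only an example, and moderators are mentioned separately.** This is true, and an analysis plan that is not shown may specify interactions. A reader might infer that the protocol rules them out; it does not. But the text ties moderation to including covariates, and the one example it gives cannot serve the purpose stated in the sentences before it. That is a wrong statement, not missing detail.

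**Site-specific effects may mean site differences in level.** The power remark fits that reading, and level controls would then be an ordinary device. However, the reference to why effects vary, and to generalising, points to the SAAF effect. If level was meant, the generalisation claim loses its basis.

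**The error rates are artefacts of the assumptions.** This largely stands. A reader might take 96.5% or 8.0% as the plan's error rates. The first is a correct finding about level, and becomes an error only if read as moderation. The second needs slopes that nearly cancel. Where sites differ in level for reasons unrelated to the factor, the control rejects in about 12% to 26% of simulated trials, but that comes from ignoring between-site variance: a site-level test on 4 degrees of freedom rejects in 4% to 5%.

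**Absolute effects do vary with level.** With a constant odds ratio of (0.05/0.95)/(0.10/0.90) = 0.474, control risks of 13.2% and 17.5% (the CPP range under Sample size, used only as an illustration) give SAAF risks of 6.7% and 9.1%, so differences of 6.5 and 8.4 percentage points. The model imposes that pattern; the control does not discover it.

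**Other parts of the plan help.** Results by authority can display site effects, and the implementation evaluation looks into reasons for differences between departments. Neither makes the regression claim correct.

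**Conclusion.** The point holds as one about model structure. A site average used as a control cannot explain variation in the SAAF effect on the model scale. This follows from algebra and needs no simulation. Its size cannot be given as one rate: in the simulations, with real effect variation present, the control was significant in anywhere from 6% to 95% of runs, depending on slopes the documents do not supply.

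Three stronger readings are not supported. First, the main result is not at risk: these models are supplementary and the primary intention-to-treat comparison is unaffected. Second, it cannot be said outright that site averages add no power: that holds if departments enter as indicators, and the protocol does not fix this. Third, generalisation does not rest wholly on this analysis: the text says only that it will help.

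The reading assumes that the effects said to vary across sites are SAAF effects, which is the more natural sense.

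**What to change.** In Inclusion of covariates:

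- Examine effect variation through a small number of arm-by-factor terms named in advance, or a random SAAF slope by site. Use worker- or team-level factors measured before randomisation; the baseline questionnaire described under Assignment of interventions covers experience and training. With six sites, the variance of a random slope will be poorly estimated.
- Keep site in these models and account for team clustering. Without the latter, the interaction test is itself anti-conservative.
- Show the six site-specific SAAF effects with intervals. Label any site-level explanation exploratory, because there are at most five site-level contrasts.
- Withdraw the statement that site-average controls explain effect variation or support generalisation. If department indicators are used, drop the site averages and the power claim for them.

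The cost is model wording; no new data are needed. The downside is a more modest claim about generalising beyond the six departments.
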